### Trial design {8}

This study is a phase I, two-arm, 1:1, randomized, triple-masked, placebo-controlled clinical trial.

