## Assignment of interventions: allocation

### Sequence generation {16a}, concealment mechanism {16b}, implementation {16c}, blinding {17a}, and unblinding {17b}

Randomization will occur within 30 days of screening by blocking within the randomization sequence, with randomization stratified by biological sex. The initial randomization series will be generated using readily available electronic random sequence generators. The randomization “code” will be created by a staff member not involved in trial operations and kept in a sealed envelope with a signature across the label and dated the day of creation. This envelope will be kept in a dedicated study folder and locked in the office of the Research Integrity Officer or designee. Thirty-two opaque envelopes will be created, sequentially numbered include a designation of the code for the assigned intervention based on the randomization sequence, and signed across the seal. Masking of the interventions (i.e., xanthohumol or placebo) will be accomplished by engaging trained staff not involved in trial operations to label product bottles based on the randomization code. Product bottles will be stored in separate locked cabinets by code and maintained in a temperature-controlled environment, with temperature logged weekly to assess environmental stability. Upon confirmation of eligibility and consent, Study Coordinators will then open the next sequentially numbered envelope at the time of randomization, the envelope number will be recorded, and allocation (As “A” or “B”) disclosed to both participant and coordinator for the first time, and the corresponding product will be removed from its locker and dispensed in the bottle to the participant. Thus, the trial will be triple-masked without PIs, co-investigators, study coordinators, or participants knowing allocation assignment of study participants. Unmasking is permissible if the DSMB requires it upon review and in the case of a serious adverse event.

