### Laboratory analysis outcomes {12}, statistical methods {20a, 20b, 20c}

Relevant laboratory-based safety measures were chosen as the primary safety outcomes, because this trial is intended to precede a clinical trial in adults with Crohn’s disease—a clinical population potentially vulnerable to anemia, liver toxicity, renal abnormalities, etc. Therefore, a formal assessment of laboratory changes in healthy humans provides critical information to guide expectations for changes in laboratory markers and associated adverse clinical effects in future research in Crohn’s and other clinical populations.

The primary objective’s laboratory-based outcome domains (and corresponding measures) are liver function (AST, ALT, alkaline phosphatase, bilirubin), renal function (BUN, creatinine, estimated glomerular filtration rate), hematology (red blood cell count, hematocrit, hemoglobin, white blood cell count), and electrolytes (sodium, potassium, calcium, chloride) measured every 2 weeks for 8 weeks. The primary outcome metric for comparison between study groups is the mean change from baseline to week 8. However, all parameters will be similarly evaluated at each follow-up time point, by formally comparing mean change from baseline to follow-up between groups. Comparisons at a single follow-up will use 2-sided independent *t* tests; omnibus tests for differing trends over time will employ linear mixed models with time point as a repeated factor and study group as an independent factor.

Primary outcome laboratory measures will be analyzed by first assessing descriptive statistics including mean, median, and standard deviation. All distributions will be tested for skew and transformed (e.g., natural log transformed) as needed to reduce the influence of skew in subsequent analyses. If inspection of distributions indicates significant non-normality that cannot be corrected with standard transformations, significance will instead be calculated using a non-parametric Wilcoxon signed rank test. The primary analysis will be a per-protocol analysis as this trial is a phase I trial focused on clinical toxicity, not a definitive efficacy or effectiveness trial; therefore, we are investigating the clinical and mechanistic effects of the product for those participants who took the experimental agent only. As a sensitivity analysis, missing laboratory data will be imputed by multiple imputation to assess the robustness of study results to imputation.

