As an element of the evaluation for safety of the intervention, the percentage of laboratory newly abnormal (for values that were within the clinically normal range at baseline) per clinical laboratory reference ranges for each lab parameter will be reported at each time point and the percentage will be compared between groups by Fisher’s exact test. Assessment for changes in the distribution of each lab parameter will be performed by presenting means and confidence intervals (CI) for the change in each group, as well as the mean CI for the difference between groups; significance will be tested using 2-sided, unpaired *t* tests (or, if inspection of distributions indicates strong non-normality, with a non-parametric Wilcoxon signed rank test) of the mean values for the xanthohumol group compared to the placebo group. Assessment for overall *increases* or *decreases* in collected parameters will be tested for linear trends of the means by linear mixed ANOVA, considered significant if *p* < 0.05, with time point as a repeated factor. This may be suggestive of evidence for cumulative toxicity if trending in a clinically deleterious direction.

Health-related quality of life, measured by PROMIS-29, is included as a tertiary measure of gross changes in health. PROMIS-29 includes 7 validated subscales (physical function, anxiety, depression, pain intensity, pain interference, sleep, social interactions), each of which will be calculated as a mean by group, and means will be compared between xanthohumol and placebo, with the primary comparison being of mean changes from baseline to week 8. Significance of changes in QOL measures will be tested according to the same plan outlined for laboratory markers, above.

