Given the small sample size of this clinical trial, changes in results related to the secondary objective including inflammatory cytokines, gut permeability biomarkers, and markers of endotoxemia are considered preliminary. Thus, our principal assessment for such exploratory outcomes will be of estimated effect sizes, calculated as a *Cohen’s d* statistic for difference between study groups, using change from baseline at each 2-week interval. The primary effect estimate will be for changes from baseline to week 8. We will also perform formal statistical comparisons with adjustments for skew as outlined in our primary objective analysis. The following will be considered evidence of possible effects for our secondary objective: (1) statistically significant effects for changes in cytokines of interest and/or (2) calculation of a Cohen’s *d* value for effect size estimation greater than 0.5 (with larger *d* indicating a larger potential effect size).

Finally, respective of our tertiary objective, we will identify and quantify xanthohumol and xanthohumol-derived metabolites in plasma, urine, and stool samples. The metabolite profile data will then be used for correlation with the time-resolved gut microbiome analysis. This approach will allow us to determine links between metabolite profiles, gut microbiome compositions, and proteomic data [29–36]. We will also quantify bile acids in plasma and stool samples as well as develop analytical methods for assessing microbiome compositional changes as appropriate to the study sample size [32, 37–49].

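### The non-parametric fallback for comparing xanthohumol with placebo is the Wilcoxon signed-rank test, a paired test that cannot compare two independent arms

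*Protocol article*

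**What the plan says.** All references are to the protocol article.

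- **Design.** Under Trial design {8}: "This study is a phase I, two-arm, 1:1, randomized, triple-masked, placebo-controlled clinical trial". The section on sequence generation says allocation is made "by blocking within the randomization sequence, with randomization stratified by biological sex". Participants in one arm are not matched to participants in the other.
- **Primary comparison.** Under Laboratory analysis outcomes {12}, statistical methods {20a, 20b, 20c}: "The primary outcome metric for comparison between study groups is the mean change from baseline to week 8".
- **Main test.** The same section states: "Comparisons at a single follow-up will use 2-sided independent" t tests. Further on it again calls the t tests unpaired.
- **Fallback, first statement.** Where transformation does not cure non-normality, "significance will instead be calculated using a non-parametric Wilcoxon signed rank test".
- **Fallback, second statement.** In the paragraph on changes in the distribution of each laboratory parameter, the unpaired t test may be replaced "with a non-parametric Wilcoxon signed rank test) of the mean values for the xanthohumol group compared to the placebo group".
- **Reach.** For PROMIS-29: "Significance of changes in QOL measures will be tested according to the same plan outlined for laboratory markers, above". For the secondary biomarkers: "We will also perform formal statistical comparisons with adjustments for skew as outlined in our primary objective analysis".

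Neither the rank-sum nor the Mann-Whitney test is named anywhere in the article.

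**The concern.** The signed-rank test ranks the absolute values of within-pair differences, or of one sample's deviations from a fixed value. It has no form for two independent samples. The second statement of the fallback therefore contradicts itself: one sentence gives an unpaired parametric test and a paired non-parametric substitute for the same contrast.

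The fallback matters because it covers primary safety measures. Liver enzymes and bilirubin are often skewed, and the protocol itself provides for distributions that transformation cannot repair. An analyst bound by the text must then deviate from it, invent pairs, or run the test the only natural way it can be run on these data: within an arm, week 8 against baseline. That last route answers a different question. It reads any change shared by both arms (season, repeated sampling, assay drift, regression to the mean) as an effect of the product.

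For the cytokines, a statistically significant change is one of the two criteria for a possible effect, so the choice of test feeds a stated decision rule.

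**Working it through.** The article gives no figure that depends on this test, so there is none to reproduce. The check has two parts.

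**1. Does the named test fit the data?**

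| Element | What the article fixes | Structure implied |
|---|---|---|
| Allocation | Two arms, 1:1, blocked, stratified by sex | Independent samples |
| Outcome | One change score per participant at week 8 | One value per person |
| Contrast | Xanthohumol against placebo | Between groups |
| Parametric test | Independent (unpaired) t test | Two independent samples: fits |
| Fallback | Wilcoxon signed-rank | Matched pairs or one sample: does not fit |

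Taking change from baseline does not create pairs across arms. It reduces each person to one value, and the two sets of values remain independent. Blocking and stratification by sex do not pair individuals either.

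**2. What happens if the text is followed?**

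Inputs: 12 per group from Sample size {14}, and 16 per arm after its allowance for 25% attrition, 12 / (1 − 0.25) = 16. Two-sided α = 0.05. The distributions and shifts below are assumptions for illustration; the article gives none.

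*(a) Pairing across unequal arms.* With 12 against 11, one participant has no partner and the test is undefined; the software returns a shape error. Unequal arms are likely, given the attrition allowance and a per-protocol primary analysis.

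*(b) Pairing across equal arms.* With 12 per arm there are 12! = 479,001,600 possible pairings and no reason to prefer one. In one simulated data set, 2,000 random pairings gave p-values from 0.27 to 1.00; the rank-sum test gives a single value, 0.80. Type I error is not inflated, because a shift common to both arms cancels in the differences (about 4% rejection under the null). Power falls: with lognormal(0, 1) data, 12 per arm and a shift of 1.0, signed-rank on arbitrary pairs rejects about 40% of the time, against about 61% for rank-sum.

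*(c) Within one arm, week 8 against baseline.* Change scores are drawn as Normal(δ, 1) in both arms with the same δ, so the product effect is zero and every rejection is false. Results from 100,000 simulated trials per cell, using exact critical values:

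| Shared shift δ (SD of change) | Signed-rank within arm, n = 12 | Signed-rank within arm, n = 16 | Rank-sum between arms, either n |
|---|---|---|---|
| 0 | 4% | 4% | 5% |
| 0.3 | 14% | 18% | 5% |
| 0.5 | 31% | 43% | 5% |
| 0.7 | 55% | 70% | 5% |

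The rank-sum column lies between 4.4% and 4.9% before rounding. It does not move with δ because adding the same constant to both arms leaves their relative ranks unchanged.

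**The case against.** The strongest reply is that this is a slip of name. The surrounding text makes the intent plain: the comparison is between groups, the t tests are unpaired, and the sentence naming signed-rank sets xanthohumol against placebo. A competent statistician would probably notice and run the rank-sum test. That is likely true, but a pre-specified plan has to name the test that will be run. The wrong one is named twice and the right one nowhere.

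Second, the rejection rates in (c) describe a misuse that the text excludes, since it asks for a between-group comparison; the other literal reading, (b), does not inflate false positives. This is fair. The figures in (c) show one way the error could do harm. They are not a property of the plan, and the shift sizes have no source in the article.

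Third, the fallback is conditional and its reach is limited. It applies only where transformation fails, and the usual log transformation may deal with much of the skew. Effect sizes are the principal assessment for the cytokines, which are called preliminary, and PROMIS-29 is tertiary. The mixed models, the Fisher's exact tests on new abnormalities, the adverse-event comparisons, the halting rules and the sample size do not depend on it. All of this stands. It limits the consequence without making the named test valid.

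**Conclusion.** The concern holds. As written, the fallback for the primary laboratory comparison cannot be run when the arms are unequal, gives a pairing-dependent answer when they are equal, and drops the placebo control if applied within an arm. This rests only on the design and the tests that the article names.

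The size of the harm depends on how the analyst resolves the contradiction. If the rank-sum test is silently substituted, there is none beyond an undocumented deviation. With arbitrary pairing, the cost is power and reproducibility. With a within-arm analysis, false-positive rates reach about 31% to 43% at an assumed shared drift of 0.5 SD and 55% to 70% at 0.7 SD (n = 12 to 16, normal change scores). Only outcomes that remain non-normal after transformation are affected, but these can include primary safety measures. The text should be corrected before any analysis.

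**What to change.** In both statements of the fallback, replace the signed-rank test with the Wilcoxon rank-sum (Mann-Whitney) test and say that it is applied to change from baseline, xanthohumol against placebo. PROMIS-29 and the secondary biomarkers then inherit the correct test without further edits.

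Two additions are optional. The Hodges-Lehmann estimate of shift with a 95% confidence interval would give an effect estimate that matches the rank test, which does not compare means. A sex-stratified (van Elteren) version would reflect the stratified allocation, although the planned t test is not described as stratified, so the plain rank-sum test is sufficient.

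The cost is a few words in two places. The sample size, visit schedule, data collection and remaining analyses do not change.

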## Oversight and monitoring

### Composition of the coordinating center and trial steering committee {5d}, data monitoring committee, its role and reporting structure {21a, 21b}

This trial is registered with ClinicalTrials.gov (NCT03735420) and includes regulatory oversight by the DSMB, FDA, the National Center for Complementary and Integrative Health (NCCIH), and the Institutional Review Boards of the National University of Natural Medicine (NUNM, approval RB9718). The DSMB will be chaired by [name], PhD and [name], of Oregon Health & Science University along with [name], DO, of Western University of Health Sciences, to ensure impartial monitoring of safety data including adverse events and laboratory markers. The board will meet on a regular basis, including at half-enrollment, to ensure monitoring of abnormal laboratory values and reporting of serious adverse events is being conducted in a timely manner. The FDA provided review and approval of the study protocol and Data Safety and Monitoring Plan (DSMP) during the Investigational New Drug (IND) application process; the FDA requested clarifications on participation criteria and halting criteria during this review. NCCIH periodically monitors trial progress via regular annual progress reports completed by the study’s Principal Investigators, evaluates progress according to a projected Study Accrual and Retention Plan (SARP), and reports from the DSMB, as well as through review and approval of all protocol modifications prior to implementation.

All study investigators will meet on a regular basis to discuss progress and developments throughout the trial. Minutes for these minutes will be maintained by the Study Coordinator, [name], and may be provided to the trial’s external auditing company upon request.

### Adverse event reporting and harms {22}

Adverse event monitoring will occur using a standardized, multi-system, 81-item adverse event questionnaire based on the National Cancer Institute’s Common Terminology Criteria for Adverse Events. The adverse event questionnaire will be administered verbally by study staff at each of the clinical visits, including the initial screening visit, with a query to determine if other symptoms not elicited by the questionnaire have been experienced. Participants will be encouraged to contact study staff between study visits if they are experiencing any new, unusual, or bothersome symptoms. Adverse events reported between study visits (i.e., not reported on the 81-item adverse event interview during scheduled visits) will be termed a “spontaneous report” adverse event and will be documented within the participant’s file by the study staff to capture the severity/grade of the report, any clinical actions taken, and the current state of the adverse event. Following a spontaneous report, the study team, in coordination with a participant’s physician as needed, will develop a response or monitoring plan, which will also be documented.

All reported adverse events, as well as the length of duration, will be reported upon trial completion with a comparison of frequency between groups. Attributability to the intervention will be determined on a case-by-case basis by the clinical investigators and DSMB members according to accounts of the event(s) in previous research, whether the symptom was present at baseline, the severity and clinical trajectory of the symptom (i.e., did it worsen with accumulated exposure), whether similar symptoms accumulated in one group vs. another, and/or if the symptom was subjectively attributed to another cause *by the participant* (e.g., wrist pain following an injury at work).

Severity of adverse events will be classified by the Clinical Investigators as grade 1 through 5 based on the following definitions: grade 1/mild (an event that requires no treatment and does not interfere with the participant’s daily activities), grade 2/moderate (an event that may cause some interference with the participant’s daily activities and/or requires medical intervention which may include over-the-counter medications), grade 3/severe (an event which limits basic self-care and/or requires hospitalization), grade 4/life threatening (an event which results in hospitalization), or grade 5/fatal (death). Adverse events will then be classified as serious or non-serious based on FDA and Federal Food Drug and Cosmetic Act definitions [50]. Adverse events will be considered serious if a participant’s outcome includes the following: a life-threatening experience, inpatient hospitalization, disability or incapacity, death, or a medical or surgical intervention to prevent one of these outcomes. All other adverse events will be designated “non-serious.” No attributable serious adverse events are anticipated during the trial unless a previously unidentified allergy is elicited by the interventional product or excipients.

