### Criteria for discontinuing or modifying allocated interventions {11b, 21b}

A participant may be withdrawn from the trial at any time they choose, due to adverse events or at their request. However, participants will be actively withdrawn if they demonstrate any new onset, moderate, or more severe adverse events attributable to the intervention. Participants will also be withdrawn if they have any critical value return on routine clinical laboratory measures of safety, including significant changes in blood cell counts, liver function tests, or renal function tests. The trial will be suspended if > 20% of study participants experience moderate or greater severity adverse events or laboratory abnormalities contributing to halting criteria including abnormal calcium, sodium, potassium, creatinine, or GFR; anemia; and/or abnormal elevations in bilirubin, elevated alkaline phosphatase, AST, or ALT that are persistent upon repeat testing.

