## Discussion

The main objective of the phase I XMaS trial is to examine the safety and tolerability of daily xanthohumol administration in healthy adults over an 8-week time frame. This objective will be accomplished by monitoring routine clinical laboratory parameters, assessing quality of life, and administering standardized adverse event queries throughout the study and using these data to make a composite assessment of clinical safety, with input from the FDA and NCCIH. Tolerability of xanthohumol will be assessed by monitoring the number and proportion of participants who discontinue the intervention citing adverse effects, changes in the seven health-related quality of life domains captured via the PROMIS-29 questionnaire, and the severity and duration of symptoms, for comparison between treatment and control groups.

Preclinical studies have demonstrated that xanthohumol has multiple therapeutic properties including modulating inflammatory pathways by acting as an FXR agonist and via inhibition of NFκB activation, regulation of gut permeability and bile acid metabolism by acting as an FXR modulator, and regulation of antioxidant protein expression via activation of NRF2 [7–13, 15, 51]. By regulating these transcription factors, xanthohumol may impact expression of numerous downstream genes in vivo and therefore has therapeutic promise for multiple disease states, including Crohn’s disease (Table 1). Furthermore, xanthohumol acts as a prebiotic for intestinal microbiota and, along with its bacterial metabolites, alters the gut microbiota [5]. Therefore, additional aims of the phase I XMaS trial are to collect data on biomarkers related to inflammation, gut permeability, bile acid metabolism, xanthohumol metabolism, and the impact of xanthohumol on gut microbiota to assess if these mechanisms are modified in vivo.

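### The grade 3 and grade 4 severity definitions both rest on hospitalisation, so an admitted non-fatal event fits two grades and a life-threatening event without admission misses the grade 4 text

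*Protocol article*

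**What the plan says.** The section Adverse event reporting and harms {22} sets out the scale and makes the definitions operative: "Severity of adverse events will be classified by the Clinical Investigators as grade 1 through 5 based on the following definitions". The two grades at issue are "grade 3/severe (an event which limits basic self-care and/or requires hospitalization" and "grade 4/life threatening (an event which results in hospitalization". Grade 2 covers some interference with daily life or a need for medical intervention, and grade 5 is death.

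The same section then sorts events into serious and non-serious by a separate list of outcomes: "a life-threatening experience, inpatient hospitalization, disability or incapacity, death, or a medical or surgical intervention to prevent one of these outcomes".

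Severity is used in three further places. The Discussion names "the severity and duration of symptoms, for comparison between treatment and control groups" among the tolerability measures. Section {22} lists severity among the factors for judging whether an event is attributable to the product. The section on discontinuing or modifying allocated interventions {11b, 21b} ties withdrawal and suspension to events of at least moderate severity.

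**The concern.** An ordinal severity scale works only if each event has one place on it. Here two adjacent grades share a defining feature, hospitalisation, and the article gives no rule for choosing between them. The higher grade is also defined by something other than what its label says, because admission is a matter of care setting and not of threat to life.

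Safety and tolerability are the primary aim, and severity is named as something to compare between arms. If two investigators can properly assign different grades to the same event, the top of the reported severity distribution cannot be read with confidence. Severity also feeds the attributability judgement, so the ambiguity carries over there as one input among several.

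**Working it through.** There is no figure to reproduce, and no arithmetic applies. The check is to run the possible types of event through the printed definitions, then trace where the answer is used.

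**Step 1: type of event against the wording**

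| Event | Grade 3 text | Grade 4 text | Grade 4 label | Serious by the separate list |
|---|---|---|---|---|
| Admitted, not life threatening, not fatal | met | met | not met | yes (admission) |
| Admitted, life threatening, not fatal | met | met | met | yes (both grounds) |
| Life threatening, not admitted | only if basic self-care is limited or admission was needed but did not occur | not met | met | yes (threat to life) |
| Fatal | superseded by grade 5 | superseded by grade 5 | superseded by grade 5 | yes |

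The first two rows show the overlap and the third shows the gap. If basic self-care was not limited and admission was not needed, the best literal fit in the third row is grade 2, by way of medical intervention. That is two grades below the label.

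**Step 2: can the verbs separate the grades?** Grade 3 speaks of an event needing admission, grade 4 of an event ending in it. In the usual case both are true. Where they part, the order runs the wrong way: an admission that was not strictly needed meets only the grade 4 wording, while an event that needed admission but did not lead to one meets only grade 3. The difference in verb gives no usable boundary.

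**Step 3: internal consistency.** The seriousness list treats a threat to life and inpatient admission as two outcomes, either of which is enough. The scale defines the first by the second. Both statements are in the same section.

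**Step 4: where the grade is used**

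- Withdrawal: "participants will be actively withdrawn if they demonstrate any new onset, moderate, or more severe adverse events attributable to the intervention". The threshold is grade 2, so grades 3 and 4 are treated alike.
- Suspension: "The trial will be suspended if > 20% of study participants experience moderate or greater severity adverse events". The threshold is again grade 2. Even a life-threatening event that fell to grade 2 because of the gap would still count under both rules.
- Seriousness: decided from its own list, not from the grade. The last column of the table is yes in every row.
- Frequency of adverse events between groups (section {22}): a count that does not depend on the grade.
- Severity between groups (Discussion) and attributability (section {22}): these do use the grade, and they are the only uses found that the defect can reach.

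**The case against.** The strongest reply is that the label belongs to the definition. An investigator who sees the words life threatening beside grade 4 will not assign it to a routine admission. Read jointly, grade 3 holds severe admissions and grade 4 holds life-threatening ones. This is a fair account of how a sensible grader would behave, and it largely removes the overlap. It does not close the gap: on the joint reading a life-threatening event without admission still fails grade 4, and no other grade describes it. It also asks the reader to treat the grade 4 parenthesis differently from the other four, each of which serves as the definition of its label.

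The second reply is that little depends on the matter, and this stands. The primary outcomes are laboratory measures. Severity by arm is promised in one general sentence of the Discussion, and the article specifies no table or test by grade.

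A reader might infer more than the text supports:

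- **That one misgraded event shifts a grade 4 row by 1/16 of an arm, about 6%.** No such row is specified. The figure also uses the maximum enrolment of 16 per arm, while the primary analysis is per protocol.
- **That the arms would be compared with bias.** Grading is planned under masking, and nothing in the article points to error in one direction.
- **That the protocol expects a serious allergic reaction which would be misgraded.** It says no attributable serious event is anticipated, and names an unidentified allergy only as an exception.

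**Conclusion.** The definitions are faulty as written. Grades 3 and 4 are not mutually exclusive for admitted, non-fatal events, and grade 4 leaves out life-threatening events managed without admission. The scale also conflicts with the seriousness criteria printed beside it.

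The consequence is minor. It is confined to the grade given to such events, in the severity comparison and in attributability judgements. It would be wrong to conclude that participant protection or the stopping rules are compromised, because withdrawal, suspension and seriousness are unaffected.

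This rests on two assumptions. Graders are taken to apply the printed definitions, as the section says they will. Hospitalised or life-threatening events are taken to be few, which is reasonable for up to 32 healthy adults (16 per arm × 2) followed over 8 weeks of dosing but is not quantified in the article.

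**What to change.** Reconcile the grade 3 and grade 4 definitions with the seriousness criteria so that each event maps to exactly one grade. One way is to define grade 4 by its own label, threat to life, whether or not the participant is admitted, and leave hospitalisation in grade 3. This uses a distinction the protocol already makes.

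No new data, visits or participants are needed, and the sample size and halting rules stay as they are. The cost is a minor amendment. The article says that modifications need NCCIH approval before implementation and that amendments go to NCCIH, the FDA and the IRBs. Since the Trial status section gives a recruitment start in August 2019, any severe or life-threatening events already graded, and any other event that may have posed a threat to life, should be re-checked against the revised wording while graders are still masked.
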